### Data Collection

The recorded characteristics and backgrounds of patients who undergo CAS and CEA will include: age, gender, and high-risk CEA characteristics (according to the Stenting and Angioplasty with Protection in Patients at High Risk for Endarterectomy trial [6]). In addition, symptom presentation and the degree of stenosis will be analyzed. Procedural success, antiplatelet use, embolic protection device (EPD) use, and the type of stent strut (open-cell or closed-cell) or patch used for CEA will be recorded, and the execution of prior post balloon dilatation at CAS (and procedure-related complications) will be analyzed to clarify the current strategy and the treatment results of both techniques. The degrees of stenosis will be measured using the method employed by the North American Symptomatic Carotid Endarterectomy Trial [2].

### Data Source and Measurement

Outcomes will be stratified by symptomatic and asymptomatic status. Symptomatic patients will be defined as having a neurological event, including any hemispheric or ocular transient ischemic attack, or major or minor stroke, that precedes the intervention ipsilateral to the treated lesion. Our definition of a symptomatic patient is the occurrence of symptoms for up to 180 days. This definition is similar to that of the Carotid Revascularization Stent Trial (CREST), although ICSS trial lesions were considered symptomatic for up to one year [1,11,12].

Technical success pertains to per-procedural events from the initiation of the procedure through the first 24-hour post operative period. Primary technical success will require the successful excision of the carotid plaque by surgical or interventional means. Technical success will be assessed by the outcomes and complications related to preoperative carotid angiograms, whenever these imaging studies are obtained prior to the carotid intervention. For CEA, primary technical success implies the successful removal of the carotid plaque and closure of the artery, with or without a patch, with less than 30% residual stenosis in the absence of stroke, MI, and death. For CAS, the introduction and deployment of the EPD and carotid stent in the absence of stroke, MI, death, surgical conversion, and vascular obstruction constitute primary technical success [13]. Secondary endpoints of interest include procedure time, blood loss, blood transfusion, clamping and shunting time, fluoroscopy time, contrast load, recovery time, range and average number of days in an intensive care unit, and length of hospital stay.

All complications will be categorized as local vascular, local nonvascular, or systemic. Complications after carotid interventions will be reported in a systematic and standardized manner with a description of the degrees of severity. Although assigning a degree of severity to all complications arising from different treatment methods may be difficult, severity scales should be provided whenever possible to allow for the assessment and comparison of adverse events. The following severity scale has been modified from the reporting standards for lower extremity ischemia established by Rutherford et al [14]: *Mild* (level 1) refers to a complication that resolves spontaneously or with minimal intervention, does not increase the length of hospital stay, and does not cause permanent disability. *Moderate* (level 2) refers to the need for significant intervention, an extension of hospitalization beyond 24 hours, and, at most, minor permanent disability that does not interfere with normal daily activity. A *severe* complication (level 3) requires major surgical, endovascular, or medical intervention, may be associated with prolonged convalescence, is usually accompanied by prolonged or permanent disability, and may result in death. Prehospital discharge data related to stroke/death will be recorded, as applicable.

When obtaining patient consent, the patient will first be approached by a doctor who is a member of the treatment team at the same hospital in which the patient will be receiving treatment. Upon obtaining patient consent, we will record the patient name, patient signature, date of signature, and the name of the doctor who introduced the study to the patient, as well as his/her professional number and signature.

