**Methods:**

This study will be a prospective 5-year analysis of treatment for atherosclerotic carotid stenosis with CEA and CAS performed at 5 centers affiliated with the Vascular Study Group at public university hospitals in Brazil. The indications for the procedures will be determined by each surgeon’s individual discretion, in accordance with preoperative risk evaluation. The primary outcome measures will be (1) any in-hospital stroke or death, and (2) any per-procedural stroke, death, or myocardial infarction (MI). Patients undergoing CEA in conjunction with cardiac surgery will be excluded from the study. Multivariate logistic regression will be performed to identify predictors of stroke or death in patients undergoing CEA and CAS. All tests of significance will be performed at the .05 level. This study was approved by the Committee of Ethics in Research at the University Hospital of Ribeirao Preto Medical School, and in all other participating institutions linked to National Research System and National Board of Health in Brazil (Process 15695/2011).

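### Primary technical success is defined inconsistently and differently for stenting and endarterectomy, so its rates cannot be compared between the two as written

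*Protocol article*

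**What the plan says.** All the defining text is in one paragraph of the protocol article, Methods, Data Source and Measurement.

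- **Time window:** "Technical success pertains to per-procedural events from the initiation of the procedure through the first 24-hour post operative period".
- **General rule:** "Primary technical success will require the successful excision of the carotid plaque by surgical or interventional means".
- **Imaging:** "Technical success will be assessed by the outcomes and complications related to preoperative carotid angiograms, whenever these imaging studies are obtained prior" to the intervention.
- **CEA:** the plaque is removed and the artery closed, "with less than 30% residual stenosis in the absence of stroke, MI, and death".
- **CAS:** "the introduction and deployment of the EPD and carotid stent in the absence of stroke, MI, death, surgical conversion, and vascular obstruction". A source (reference 13) is cited at this point.

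Two other places bear on it. Data Collection lists procedural success and EPD use among the items recorded. The Results section says that stenting done with embolic protection goes to the CAS group, and says nothing about stenting without it.

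**The concern.** The general rule mentions interventional means, so it is meant to cover stenting. Yet it demands something that the CAS definition does not. A centre coding this field has two rules for the same CAS patient, and the text does not say which one governs.

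The criteria also differ by technique in ways that the procedures themselves do not force, and the imaging named comes from before the procedure. The article's Introduction sets the main objective as evaluating quality of treatment by analysing both techniques. A reader who meets two technical success rates in the report will naturally compare them. At stake is whether such a difference describes the procedures or partly the wording of the two definitions.

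**Working it through.** The article gives no rate, difference or power for technical success, so there is no figure to reproduce. The check is a comparison of the text, followed by an illustration on stated assumptions.

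**Step 1. Criteria side by side (Data Source and Measurement)**

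| Element | General rule | CEA definition | CAS definition |
|---|---|---|---|
| Excision or removal of plaque | required | required | not mentioned |
| Residual stenosis below 30% | not mentioned | required | not mentioned |
| EPD deployed | not mentioned | not applicable | required |
| No surgical conversion | not mentioned | not applicable | required |
| No vascular obstruction | not mentioned | implied by the 30% limit | required, term not defined |
| No stroke, MI or death | not mentioned | required | required |

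The first row is a contradiction between the general rule and the CAS definition. The second and third rows are criteria that one technique carries alone. An endarterectomy that leaves 50% stenosis fails. A stent that leaves 50% passes, unless that narrowing counts as the undefined vascular obstruction.

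**Step 2. Imaging against time window**

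The window opens when the procedure starts and closes 24 hours after the operation. An angiogram taken before the procedure lies outside it and cannot show residual stenosis, stent deployment or a later obstruction. The paragraph names no post-procedure imaging for the 30% limit.

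**Step 3. Status of the EPD**

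EPD deployment is a condition of CAS success (Data Source and Measurement). EPD use is a recorded variable (Data Collection). Protected stenting is what goes into the CAS group (Results). An unprotected stent could therefore be a CAS failure, a CAS case with that variable recorded as absent, or outside the CAS group.

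**Step 4. How large a gap the definitions alone could make**

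Assumptions, none of them in the article: both techniques perform equally; a share s fails on stroke, MI or death (2% or 5%); a criterion applied to one technique only fails a further share q of its remaining cases (2%, 5% or 10%).

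Success without the extra criterion is 1 − s, and with it (1 − s)(1 − q). The gap is (1 − s) × q.

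- q = 2%: 0.98 × 0.02 = 0.0196; 0.95 × 0.02 = 0.0190
- q = 5%: 0.98 × 0.05 = 0.0490; 0.95 × 0.05 = 0.0475
- q = 10%: 0.98 × 0.10 = 0.0980; 0.95 × 0.10 = 0.0950

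The gap is thus about 2, 5 and 10 percentage points.

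**Step 5. Would such a gap look significant if someone tested it?**

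Inputs: about 800 cases and a .05 level (Statistical Analyses). A two-sided test and the splits below are assumptions, since the article gives no split. Chance of significance = Φ((d − 1.96 × SE0) / SE1), where d is the gap, SE0 the standard error with the pooled proportion and SE1 the unpooled one.

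Example with 400 v 400, s = 2%, q = 5%: d = 0.049, SE0 = 0.01458, SE1 = 0.01448, so Φ((0.049 − 0.02858) / 0.01448) = Φ(1.41) = 0.92.

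| Split (without v with the extra criterion) | q = 2% | q = 5% | q = 10% |
|---|---|---|---|
| 400 v 400 | 20–37% | 73–92% | over 99% |
| 600 v 200 | 19–36% | 65–86% | 98–99.7% |
| 200 v 600 | 14–22% | 56–80% | 98–99.9% |

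In each cell the lower value is for s = 5% and the higher for s = 2%.

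**The case against.** The strongest reply is that these are wording slips in a minor, descriptive outcome. Technical success is not among the primary outcomes in the Abstract, is not in the list of secondary endpoints that closes the same paragraph, and has no stated test between techniques. Some technique-specific elements are legitimate: conversion to surgery can only happen to a stent procedure. The CAS definition is credited to a cited source. All of this stands, and it limits the weight of the point. It does not make the paragraph usable as written.

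Several stronger readings are tempting, but the article does not support them.

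- **Every stent fails, so CAS success is 0%.** This takes one sentence alone. CAS has its own definition without excision, so the fault is a contradiction.
- **The comparison is settled by definition and not by performance.** Both definitions share stroke, MI and death, so performance counts.
- **CEA has no occlusion criterion.** An occluded artery cannot have less than 30% residual stenosis, so it already fails.
- **Patients without a preoperative angiogram go unassessed, which selects a subset by technique.** The imaging sentence can also be read as counting complications of a diagnostic angiogram when one was done. It is unclear, and a restricted denominator is inference.
- **Unprotected stents put a fixed penalty on CAS.** The Results wording may place them outside the CAS group.
- **Stroke, MI and death must come out because they repeat the primary outcomes.** Overlap in a descriptive composite is a matter of preference, not an error.

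**Conclusion.** The point holds in limited form. Three defects can be read directly from the text: the excision rule conflicts with the CAS definition; the imaging named cannot establish a post-procedure result; and the residual-stenosis limit applies to CEA only. To these is added an EPD condition for CAS whose relation to group membership is unclear. Following the paragraph as written gives contradictory coding, and rates that are not comparable between techniques.

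The numerical effect is unknown, because the article gives no failure rates. The gap of about 2 to 10 points rests on the assumption of equal performance and one-sided failure of 2% to 10%. At 2% the effect is small; from about 5% it could pass for a real difference if tested. Because CEA and CAS each carry a criterion of their own, the direction cannot be predicted. The primary outcomes are untouched.

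**What to change.** 1. Delete the general excision sentence, or reword it so that it agrees with the technique-specific definitions.
2. Replace the reference to preoperative angiograms with the post-procedure imaging that the centres already obtain.
3. Apply the residual-stenosis criterion to both techniques, or to neither if such imaging is not routine in one of them.
4. Report EPD deployment as a separate item, and reconcile its role in the success definition with Data Collection and the Results section, stating where unprotected stenting is counted.
5. If the criteria are not aligned, report technical success within each technique only and do not compare the rates.

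The cost is a change of endpoint wording; no new procedure is needed. The article does not say which post-procedure images are routine, so the centres must confirm this before item 3 is settled. Aligned criteria lose some direct comparability with the cited source, and reporting its definition as a supplement covers that.

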### Researcher Responsibilities, Institutions, and Sponsors

The principal investigators are committed to continuing the project over time while ensuring the accuracy of the information. Data will be collected from the routine diagnostic tests and specific treatment at each institution. There will be no project sponsor external to the universities.

The recruitment information will be available from the participating hospitals via an online document available to participants. In addition, the analytical procedure will include bimonthly meetings of the group of doctors responsible for the study, along with the respective principal investigators, to observe the progress of the project and evaluate the partial and total data, in addition to writing the manuscript.

## Results

The study is in the recruitment phase, and we are enrolling patients at 5 centers in Brazil. It is anticipated that 800 patients will be recruited to the study by the end of 2018. Analyses will focus on primary end points for patients that are allocated to each treatment group. During the per-procedural period, the occurrence of the primary end point components (stroke, MI, or death) for CAS and CEA will be analyzed for symptomatic or asymptomatic subjects. The median time from randomization to the procedure will be compared for CAS and CEA. Stenting with embolic protection of patients will be assigned to the CAS group. General or local anesthesia of patients will be assigned to the CEA group. The median duration of follow-up will be determined. During that time, the level or prevalence of selected risk factors will be analyzed to determine if they remained similar between the two treatment groups.

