## Methods

### Patient Population and Setting

The CEA and CAS registry in Brazil (part of RHEUNI) is being used as a prospective observational study in Brazil, and has been conducted since July 2013. Final data analyses are expected in July 2018 from the 5 public university hospitals of the São Paulo state that provide vascular therapy. Several consecutive procedures will be registered as CEA or CAS by certified vascular surgeons from 5 centers (University Hospital of Ribeirão Preto Medical School of University of São Paulo, University Hospital of School of Medical Sciences of University of Campinas, University Hospital of Marilia Medical School, University Hospital of Botucatu Medical School, and University Hospital of São Jose do Rio Preto Medical School). All participating vascular surgical centers have extensive experience in the treatment of carotid disease, and they are all training centers of reference in Brazil. The ethical committee of each hospital has approved this project.

Inclusion criteria are as follows: patients with carotid atherosclerotic stenosis >70% who underwent CEA or CAS for the treatment of carotid stenosis at any of the 5 hospitals involved in the study, male or female, and >18 years of age. Carotid stenosis is defined as (1) stenosis >70% by catheter angiography (North American Symptomatic Carotid Endarterectomy Trial criteria) or (2) by Doppler ultrasound with >70% stenosis defined by a peak systolic velocity of at least 230 cm/second, plus at least one of the following: an end diastolic velocity >100 cm/second, or internal carotid/common carotid artery peak systolic velocity ratio >4.0, or computer tomography with >70% stenosis, or magnetic resonance with >70% stenosis. Exclusion criteria include cases of concomitant cardiac surgery, carotid dissection, fibromuscular dysplasia, or trauma.

RHEUNI data have been validated for completeness by quarterly audits of discharge claims data from each participating institution. These audits ensure complete inclusion of all consecutive procedures performed at the participating hospitals.

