One meta-analysis pooled data from 13 prospective, randomized, or controlled clinical trials that compared CEA with CAS [18]. With combined data from all trials, over 7000 patients were included, the majority of whom (79%) were symptomatic. The post operative risk of stroke and death over the subsequent 30 days was higher in the CAS group compared with the CEA group (odds ratio [OR] 1.57, *P*=.01) and was highest in symptomatic patients (OR 1.89, *P*=.01). EPDs used with CAS did not significantly reduce the 30-day per-procedural risk of stroke/death related to CEA, but they did decrease the 30-day risk of stroke/death compared to that associated with CAS without an EPD (2.7% vs 7.5%, OR 0.34, *P*<.01). In contrast, CAS was associated with a lower risk of cranial neuropathy (OR 0.06, *P*<.01) and a lower risk of post operative MI (OR 0.43, *P*<.01). Based on these findings, the authors advocated reserving CAS for revascularization in patients with anatomical conditions that make CEA difficult or place patients at higher risk for cranial nerve injury (such as restenosis after prior CEA), or in patients with concomitant significant carotid artery disease. The limitation of CAS to specific patient groups is outlined in both the Society of Vascular Surgery and European Society of Vascular Surgery guidelines, particularly for those at high risk for CEA and in, “high-volume centers with documented low per-procedural stroke and death rates or inside a randomized clinical trial” [19,20].

Some other important studies are underway. In response to the growing uncertainty regarding clinical management of asymptomatic patients with carotid artery disease, the National Institutes of Health is financing the CREST-2 trial. This multicenter, randomized study has two arms related to intervention: CEA versus best medical therapy (BMT) and CAS versus BMT. Patients can opt to enroll in either the CEA or CAS arm. Randomization, therefore, determines whether a patient undergoes an intervention or BMT, rather than the type of intervention (CEA or CAS). Patients allocated to CEA or CAS treatments will also receive the same BMT as those randomized to medical treatments. The study is expected to take approximately 10 years to complete randomization, and produce results for at least 4 years of follow-up [21].

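### The sentence assigning stenting with embolic protection to the CAS group conflicts with the Methods and leaves unprotected stenting without a group

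*Protocol article*

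**What the plan says.** In the protocol article, Results, the sentence on the stenting group reads "Stenting with embolic protection of patients will be assigned to the CAS group". The next sentence has the same form for surgery: "General or local anesthesia of patients will be assigned to the CEA group". The article has no other sentence worded as an assignment to the CAS group. The same paragraph says that the primary end points will be analysed for patients as allocated to each treatment group.

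Four statements in the Methods bear on the same question:

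- Patient Population and Setting includes patients "who underwent CEA or CAS for the treatment of carotid stenosis at any of the 5 hospitals involved in the study". There is no EPD condition, and procedures are registered simply as CEA or CAS.
- The same section says of the quarterly audits: "These audits ensure complete inclusion of all consecutive procedures performed at the participating hospitals".
- Data Collection lists among the items to be recorded "Procedural success, antiplatelet use, embolic protection device (EPD) use".
- Data Source and Measurement defines primary technical success for CAS as "the introduction and deployment of the EPD and carotid stent in the absence of stroke, MI, death, surgical conversion, and vascular obstruction".

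The Discussion cites a meta-analysis of 13 trials. It reports that EPDs did not significantly reduce the 30-day risk relative to CEA, "but they did decrease the 30-day risk of stroke/death compared to that associated with CAS without an EPD" (2.7% vs 7.5%, OR 0.34).

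**The concern.** EPD use is a feature of how the stenting was carried out. If it decides who counts as a CAS patient, the group is defined by something that happens during the procedure and that the article itself links to stroke and death. The surgical group has no comparable filter, because general or local anaesthesia covers essentially every endarterectomy.

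Both primary outcomes in the Abstract are at stake: in-hospital stroke or death, and per-procedural stroke, death or MI. Dropping unprotected stents from one arm would make the CAS rate describe protected stenting only, while the stated aim is a real-world comparison of CAS and CEA. The Discussion also reports a suggestion that protection methods be chosen according to preoperative risk. On that view, the omitted cases would not be a random subset.

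**Working it through.** **1. The texts side by side.**

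| Question | Results | Methods |
|---|---|---|
| Is an EPD needed to be in the CAS group? | Yes, read literally | No: the inclusion rule has no EPD condition |
| Can a CAS case lack an EPD? | No group is named for it | Yes: EPD use is recorded as a variable, which is informative only if it varies |
| What is a CAS case without EPD deployment? | Not described | A CAS case that did not reach technical success |
| What is a CAS case converted to surgery? | Not described | Also short of CAS technical success; its group for the primary outcomes is not stated |

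The literal reading of the Results and the Methods cannot both govern the same analysis.

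**2. Check of the cited figure.** The inputs from the Discussion are 30-day stroke/death of 2.7% with an EPD and 7.5% without.

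OR = (0.027/0.973) / (0.075/0.925) = 0.342

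This agrees with the stated 0.34.

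**3. Size if unprotected stents were left out.** Let u be the unprotected share of all CAS. The documents do not give u, so it is an assumption shown over a range.

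- Rate for all CAS = 0.027(1 − u) + 0.075u
- Rate for protected CAS only = 0.027
- Understatement = 0.075u − 0.027u = 0.048u

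| u (assumed) | All CAS | Protected only | Understatement (points) | Share of the all-CAS rate |
|---|---|---|---|---|
| 0 | 2.70% | 2.70% | 0 | 0 |
| 5% | 2.94% | 2.70% | 0.24 | 8% |
| 10% | 3.18% | 2.70% | 0.48 | 15% |
| 20% | 3.66% | 2.70% | 0.96 | 26% |
| 30% | 4.14% | 2.70% | 1.44 | 35% |
| 50% | 5.10% | 2.70% | 2.40 | 47% |

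**4. What cannot be computed.** The documents give no event rate and no frequency for failed or converted CAS, so no figure is attached to those cases.

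**The case against.** The strongest reply is that the sentence is not an analysis rule. It stands in the Results, not in Patient Population and Setting or Statistical Analyses. Its companion on anaesthesia separates no surgical patient from another and can only describe technique. The sentence before the pair speaks of time from randomization, although the Methods call the study observational, so the paragraph is loosely worded throughout. On this view the Methods passages show that no exclusion is intended. This is a plausible reading, and it is why the bias is stated as conditional. It does not remove the conflict: the sentence speaks of assignment, and an analyst who looks for the definition of the CAS group finds no other sentence in that form. The reference to allocated patients does not settle it either, because the choice of procedure is left to the surgeon and nothing is allocated by design.

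A second reply concerns the numbers, and it stands. The cited trials compared CEA with CAS, so the contrast between CAS with and without an EPD may be confounded. It is a 30-day rate in a population that was 79% symptomatic, whereas the first primary outcome here is in-hospital and results are stratified by symptom status. The unprotected share may be small or zero. The figures therefore show direction and order of magnitude only.

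A reader might go further and infer that failed or converted stenting also leaves the CAS group, or that conversions are moved to CEA and penalise it. The documents do not support this. The technical-success definition treats conversion as a failure of CAS, which suggests that such a case is still viewed as a CAS case, and no passage moves it to CEA.

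Finally, detailed crossover rules and sensitivity analyses may properly sit in a fuller document. Their absence from the article is not the point made here; the point is a stated sentence that conflicts with other stated text.

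**Conclusion.** The inconsistency is real and should be removed before analysis. The literal wording in the Results ties the CAS group to EPD use, against an inclusion rule without that condition, audited consecutive inclusion, and the recording of EPD use as a variable.

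If the sentence were applied as written, the CAS stroke/death rate would be understated by about 4.8 percentage points times the unprotected share: nothing at u = 0, about 0.5 points at 10%, 1.0 at 20% and 1.4 at 30%. This rests on three assumptions: that unprotected stents are in fact omitted, that u is above zero, and that the cited 2.7% and 7.5% carry over to these five centres. The documents establish none of them, so it cannot be said that the CAS rate is biased, only that it would be under that reading. No bias from converted cases is asserted.

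This is a correction worth making because group membership feeds both primary outcomes, but the ambiguity does not by itself undermine the study.

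**What to change.** Reconcile the Results sentence with the Methods by replacing it with a rule for the analysis groups. For the primary outcomes, each patient is analysed in the group of the procedure first attempted (CAS or CEA), regardless of EPD use, completion or conversion. Report EPD use as a descriptor of the CAS group. An analysis restricted to protected stenting can be added as a sensitivity analysis if wanted.

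The cost is about one sentence. EPD use is already on the list of recorded items, and the audits are said to capture all consecutive procedures, so including unprotected cases needs no new data. The procedure first attempted must be identifiable in the registry for converted cases. No treatment changes. The one downside is that the reported CAS rate may be less favourable than a protected-only rate.
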